#### Sample size

Our sample size was calculated to detect a difference in the percentage of residents prescribed ≥800 IU/daily vitamin D at follow-up in the intervention versus control groups. We assumed an average of 120 residents per LTC home and that 30% of residents were prescribed ≥800 IU/daily vitamin D at baseline [33]. We postulate a 20% increase in vitamin D prescribing in the intervention group and a 5% increase in the control group (to account for the potential impact of other province-wide initiatives such as the *Ontario Osteoporosis Strategy for LTC*). Based on these assumptions, to detect a 15% difference in prescribing between the groups with an intracluster correlation of 0.10 (two-sided test with significance = 0.05), a sample size of 2,160 residents from 18 LTC homes in each of the intervention and control groups is required to achieve 82% power. Factoring in a potential 10% dropout rate, the recruitment target was 40 LTC homes (20 = intervention, 20 = control).

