### Study outcomes

#### Feasibility

Feasibility outcomes are measured at the facility-level and include (some are only relevant to intervention homes): the proportion of homes that are recruited and retained, attendance of Medical Directors and other professionals at educational sessions, internal champions identified, action plan items identified and initiated, performance reports provided and reviewed, falls and fracture data collection completed. A criterion of ≥80% will be used as the criterion for success on each of these feasibility measures, with the exception of recruitment. Other cluster randomized controlled trials (RCTs) in nursing homes aimed at changing the behaviour of health professionals have noted recruitment in the 40 to 50% range [38-40], thus our recruitment criterion for success was 40%.

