#### Randomization and consent

Stratified block randomization was used to randomly allocate LTC homes to the intervention or control arm of the study (recruitment is now closed). LTC homes were stratified based on home size and profit/non-profit. Profit status was taken into consideration because there is some evidence that the quality of care is higher in non-profit homes compared to for-profit homes [43-45]. The allocation sequence was computer generated using nQuery 6.0 software by an off-site research member who is not involved in the recruitment, enrollment of clusters, or data analysis. Once the appropriate representative from the home was consented, the independent member assigned intervention and control groups based on the sequence and notified the coordinating centre. Because the homes are not blinded to treatment arms, the homes were informed of their allocation.

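### The assumptions in the Sample size section give about 80% power with 18 homes per arm, not the stated 82%

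*Protocol article*

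**What the plan says.** All the inputs are in the Sample size section of the protocol article. On home size and starting level it says: "We assumed an average of 120 residents per LTC home and that 30% of residents were prescribed ≥800 IU/daily vitamin D at baseline". It then postulates that prescribing rises by 20 points in intervention homes and by 5 points in control homes, calls the result a 15-point difference, and takes an intracluster correlation of 0.10 with a "two-sided test with significance = 0.05". From these assumptions it concludes that "a sample size of 2,160 residents from 18 LTC homes in each of the intervention and control groups is required to achieve 82% power". The allowance for loss follows: "Factoring in a potential 10% dropout rate, the recruitment target was 40 LTC homes", that is 20 per arm.

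Three other places bear on the point. Under Study population, the homes actually randomised are 19 intervention and 21 control. Under Randomization and consent, "LTC homes were stratified based on home size and profit/non-profit". Under Quantitative analysis, the comparison is by generalized estimating equations (GEE) with an exchangeable correlation structure and the home as the cluster.

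**The concern.** The paragraph presents 82% as the consequence of assumptions it has just listed, so a reader should be able to recover it from them. The rises must be absolute, because only then do they differ by 15 points, so the follow-up comparison is 50% v 35%. At those rates the usual formulae fall short of 82%, all in the same direction, so rounding does not explain the difference.

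What is at stake is modest. Vitamin D prescribing is the primary clinical outcome, and the Discussion offers the trial's effect sizes and intracluster correlation as a guide for later studies. Someone planning such a study may take over this calculation, and would then inherit either a wrong power or an unstated control rate.

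**Working it through.** **Inputs (Sample size section).** Residents per home m = 120; homes per arm k = 18; residents per arm 18 × 120 = 2,160, as stated; intracluster correlation 0.10; two-sided α = 0.05. Control rate 30 + 5 = 35%; intervention rate 30 + 20 = 50%; difference 0.15.

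**Effective sample size.** Design effect = 1 + (m − 1) × ICC = 1 + 119 × 0.10 = 12.9. Effective n per arm = 2,160 / 12.9 = 167.4.

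**Power at the stated rates, 35% v 50%.** Unpooled SE = √[(0.35 × 0.65 + 0.50 × 0.50) / 167.4] = √(0.4775 / 167.4) = 0.0534. Ratio = 0.15 / 0.0534 = 2.81.

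| Method | Power |
|---|---|
| Unpooled normal: Φ(2.81 − 1.96) | 80.2% |
| Pooled variance under the null, unpooled under the alternative | 79.6% |
| Arcsine | 79.6% |
| Log odds ratio, Wald | 78.9% |
| Unpooled, noncentral t on 36 − 2 = 34 df | 77.9% |
| Continuity-corrected | 76.2% |

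None of these reaches 82%. The closest is 1.8 points below it. To reach 82% at these rates takes 18.9 homes per arm (unpooled) or 19.2 (pooled).

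**What does give 82%.** Keep the 15-point difference but start from the baseline rate, so 30% v 45%. SE = √[(0.30 × 0.70 + 0.45 × 0.55) / 167.4] = √(0.4575 / 167.4) = 0.0523; ratio 2.87; power 81.9% (unpooled) or 81.2% (pooled). Using the control variance, 0.35 × 0.65, in both arms at 35% v 50% also comes out at 82.1%. The first route uses only numbers in the paragraph and a standard formula, so it is the more natural explanation. The document does not say which was used.

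**Dropout step.** 18 / 0.90 = 20 per arm, 40 in total. This is correct.

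**Homes actually randomised, none lost (19 intervention v 21 control).** Effective n = 19 × 120 / 12.9 = 176.7 and 21 × 120 / 12.9 = 195.3. SE = √(0.25 / 176.7 + 0.2275 / 195.3) = 0.0508; ratio 2.95; power 84.0% (normal) or 82.1% (t, 38 df).

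**Unequal home sizes.** The article gives no coefficient of variation (CV), so 0.3 to 0.6 is an assumed range. Exchangeable GEE weights homes nearly equally when m × ICC is large. Its relative efficiency is about 1 − CV² × L × (1 − L), with L = m × ICC / [1 + (m − 1) × ICC] = 12 / 12.9 = 0.930. At CV 0.6 this is 1 − 0.36 × 0.930 × 0.070 = 0.977.

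| Assumed CV | Normal, unpooled | t, 34 df |
|---|---|---|
| 0 | 80.2% | 77.9% |
| 0.3 | 80.0% | 77.7% |
| 0.4 | 79.8% | 77.5% |
| 0.5 | 79.6% | 77.2% |
| 0.6 | 79.3% | 76.9% |

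The loss is at most about 1 point.

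**The case against.** The strongest reply is that this is too small to matter. The unpooled formula gives 80.2%, within 2 points of the stated value. The section names no test or small-sample correction, so the t reference is a reviewer's choice and leaving it out is no arithmetic error. The trial is described as a pilot designed mainly to assess feasibility, recruitment is closed, and a null result will be read from its 95% confidence interval. With all 40 homes retained, power is at or above 82% by either reference.

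Most of this stands, and it limits the point to a minor one. It does not rescue the label: the section attaches 82% to 18 homes per arm and to assumptions that give about 80% even by the most favourable standard formula tried.

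Two stronger readings are tempting, and the documents support neither.

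- *Variation in home size cuts power to between 66% and 77%.* That range comes from the design effect 1 + [(1 + CV²) × m − 1] × ICC, which gives every resident equal weight. The planned analysis is exchangeable GEE, for which the loss is about 1 point. Stratifying on size shows that homes differ, not by how much, and 120 is given as an average.
- *The retention criterion conflicts with the dropout allowance.* The Feasibility section says "A criterion of ≥80% will be used as the criterion for success on each of these feasibility measures, with the exception of recruitment", which covers retention, while the sample size allows for 10% loss. The first is a threshold for judging feasibility and the second is a planning allowance. They serve different purposes and need not agree.

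**Conclusion.** The stated power is wrong as written, by a small amount. On the plan's own assumptions, with 18 equal-sized homes per arm, power is about 80% by the normal formulae, roughly 2 points below the figure given. It is about 78%, 4 points below, if the 34 degrees of freedom are respected. That the control rise was omitted from the variance is a plausible inference from the match at 30% v 45%, not something the article states. The results rest on reading the rises as absolute, which the 15-point difference requires, and on taking the intracluster correlation of 0.10 as given.

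This is a correction to a reported figure. It is no evidence that the trial is undersized.

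**What to change.** Do one of two things in the Sample size section:

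- restate the power for 18 homes per arm at 35% v 50% as about 80%, adding that it is about 78% with a t reference on 34 degrees of freedom; or
- keep 82% and state the two rates and the formula that produce it.

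Optionally add the power for the 19 and 21 homes randomised: about 84% (normal) or 82% (t) if all are retained. If an allowance for unequal home sizes is wanted, take the CV from the bed counts already collected as facility-level data and apply the relative efficiency of exchangeable GEE, not the size-weighted design effect.

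The cost is one sentence and a slightly less favourable figure. The design, the number of homes and the analysis stay as they are.

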#### Ethical considerations

The study was approved by the Hamilton Health Sciences/McMaster University Faculty of Health Sciences Research Ethics Board. A representative from the home provided initial consent prior to randomization, and each PAC team participant provides written informed consent at the first educational session.

## Discussion

KT research in LTC is still in its early stages [4-6]. Our project is one of the first RCT studies to examine the effectiveness and feasibility of a multifaceted, interdisciplinary KT intervention in LTC. Given that this is a pilot RCT, feasibility measures such as recruitment and retention, attendance at educational sessions by PAC members, and use of study materials are important outcomes for planning future interventions. Furthermore, results from the upcoming qualitative phase of the pilot study will provide valuable information about the KT-related needs of health professionals working in LTC. It will also assist us in gaining some preliminary data on what may be the most active ingredients of the complex intervention. A better understanding of these factors will enable future researchers and care providers to select and tailor KT strategies that can maximize the uptake and utilization of evidence in LTC.

Increasing the utilization of available evidence by clinicians in daily practice is difficult in any setting, and the LTC environment presents some additional unique challenges. Prescribing for the frail elderly is especially challenging due to the presence of co-morbid illness, frequently large number of medications, functional impairment, cognitive deficits, and age-associated decline in renal function [72-74]. The majority of practice guidelines do not adequately address the challenges of applying recommendations to elderly patients, particularly those with co-morbidities [75]. In addition, the composition and skills of the nursing staff in LTC are different than in other sectors because nurse’s aides provide most of the direct care and their care rituals are often focused on task completion [19].

Implementing evidence-based practices in LTC is made more complex by the fact that the physicians are not typically located at the LTC home. Instead they rely on the on-site healthcare team to inform and update them about their patients' conditions. Clinical leaders are often registered nurses (as opposed to physicians in acute or primary care settings) [76], and they assume greater responsibility for the coordination, decision-making, and administration of drug-related interventions [77].

Heavy paperwork and institutional requirements, limited resource and staffing levels, limited time to implement protocols, the absence of a learning culture, entrenched ways of learning and communicating, ‘change fatigue,’ and high staff turnover are other postulated factors that inhibit the uptake of evidence-based practices [6,20,78,79]. In a study of registered nurses working with the elderly [80], the most commonly noted barriers to research use were the lack of a cadre of knowledgeable colleagues with whom they could discuss research issues, facility-level barriers, the lack of time to read research studies and the fact that research findings are not readily available in a single location. These nurses believed that establishing networks among colleagues, staff, researchers, and physicians would enhance the uptake of research evidence.

If the above challenges can be addressed, there are elements in the LTC environment that also make it conducive to implementing best practices. For example, as noted by Berta *et al.*[6] LTC homes are ‘small, structurally flat, and highly reliant on collaborative decision making’; thus decision makers and staff in LTC may be more amenable to implementing complex innovations than in other practice settings.

The design and implementation of our intervention was founded on the well-known Canadian Institutes of Health Research Knowledge-to-Action cycle [60]. In this paper, we describe how our intervention is adapting knowledge to the local context (LTC homes in Ontario) and continuously assessing barriers and facilitators to knowledge use. Despite the importance of tailoring the intervention based on identified barriers, recent evidence suggests that many studies do not effectively do this [81]. We have tailored the intervention to better meet the needs of LTC care providers by incorporating our educational sessions within regularly scheduled PAC team meetings, developing the reminders and point-of-care tools in partnership with front-line LTC providers, and engaging staff in identifying their own site-specific strategies needed to address barriers (*e.g.*, action planning). We are monitoring knowledge use throughout the study via the performance reports and action plans completed on site and evaluating outcomes using quantitative, qualitative, and process measures. Through ongoing work with internal champions, our partner pharmacy provider, and our website forum (http://www.osteoporosislongtermcare.ca[54]), we have built in sustainability mechanisms. A Swedish study [18] that examined whether nurses who continued continuous quality improvement (CQI) activities over several years emphasized that supportive leadership and access to individuals with research expertise were key factors in sustained evidence-based practice.

Our design elements are also congruent with recommendations from the Nursing Home Quality Initiative launched in 2002 by the Centers for Medicare and Medicaid Services in the United Stated [58]. Lessons learned about implementing CQI in LTC included: forming partnerships with LTC stakeholders, engaging physicians and Medical Directors in the CQI process, teaching CQI principles to all LTC staff, facilitating the exchange of successful strategies and practical tips among LTC homes, and providing one-on-one assistance to LTC staff and administrators. Frequent contact with and involvement of the entire CQI team were identified as essential to overcoming problems stemming from high staff turnover and heavy workload demands on Administrators and Directors of Nursing [58]. ViD*OS* has taken this advice and worked closely with the entire PAC team, including Medical Directors, to develop and update action plans to improve bone health of LTC residents.

Certainly one of the frequently asked questions regarding multifaceted interventions is: which components of the ‘black-box’ are most effective? Although we cannot answer this question quantitatively, we will attempt to address this issue in the qualitative phase of the study by asking participants how effective they perceived the various elements of the ViD*OS* intervention to be, and what individual and organizational factors they believe facilitated or inhibited the change process.

The lessons learned from this pilot RCT will be helpful when planning future KT research on other health issues in LTC settings. This includes insights on the KT process (*e.g.*, recruitment and retention of leaders in innovation), resources (time and budget issues), management (personnel and data management issues), and scientific evidence (effect sizes, intracluster correlation) [42]. It is anticipated the final results of this study will be presented in 2013.

## Abbreviations

(ViD*OS*): Vitamin D and Osteoporosis Study; (LTC): Long-term care; (KT): Knowledge translation; (PAC): Professional advisory committee; (CIHR): Canadian Institutes for Health Research; (CQI): Continuous Quality Improvement; (KTA): Knowledge to action; (PDSA): Plan Study Do Act; (RCT): Randomized Controlled Trial.
